## Methods

### Study design and setting

This study is designed as a prospective, two-arm parallel-group, multi-center, open-label, randomized-controlled clinical trial (phase III trial). It will be conducted at the Department of Gynecology and Obstetrics of the University Medical Centre of the Johannes Gutenberg University Mainz, Germany, as well as the department of Gynecology and Obstetrics at the St. Josef’s Hospital, Wiesbaden, Germany. All data will be recorded pseudonymized. Only the principle investigator of the study, as well as the study nurses in charge will have access to the pseudonymization list in case of adverse events or trial termination.

The active fasting period will be conducted for three months during CHT. Participants will be scheduled for study visits during their routine care (d1 of each cycle) and routine laboratory visits on days 8 (and 15 in three week cycles) of each cycle during the three months of the active trial period. Additional study visits will be scheduled for nutritional counseling prior to the start of the chemotherapy as well as a follow up visit at six months (**Table 1**). QoL including fatigue assessment will be performed at baseline, each week during the 12 weeks active trial period as well as at the six months follow-up. Specific quality of life aspects regarding sleep quality and pelvic floor function will only be assessed at baseline, after three months and after six months.

**Table 1 T1:** Visit overview and outcome measures assessed during each study visit.

Timepoint	Study period						
	t_-1_ *(3d - 4w prior to CHT)*	All cycles d_1_	All cycles d8	3-week cycles day 15	12 weeks after Start CHT ( ± 1 week)	Post surgery where applicable	6 months follow up ( ± 2 weeks)
Enrolment Eligibility screen Informed consent Randomization Allocation	XXXX						
Interventions Intermittent fasting Normal diet Nutritional counselling	XXX				→ →		Voluntary continuation of IFSwitch to IF possible
Assessments Demographics Medical history Current medication Anthropometric measurements Vital signs Physical examination CTCAE Hematogram Glucose/ketone levels Organ Blood panely-H2AX DNA damage essayImmunological responseTumor response Tumor markers Pathological response Radiological response	XXXXXXXXXXX(X)^3^	XXXXXXXXX^1^	XX^2^	X	XXXXXXXXX(X)	X	XXXXXXXX(X)

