### Recruitment and randomization

Patients will be recruited at the time of diagnosis and discussion of the treatment plan after the interdisciplinary tumor conferences of each hospital had finalized the treatment schedule. Written informed consent will be obtained from all participants prior to randomization and baseline visit. Patients can withdraw consent and effectively withdraw their trial participation at any point without any disadvantages. A screening checklist including all inclusion and exclusion criteria will be assessed by a medical doctor prior to randomization. Variable block randomization stratified by tumor entities and study site will be used to randomly assign participants to intervention or control group (1:1). Block length will be disclosed upon completion of the trial. The preparation of the randomization lists will be performed by a statistically trained researcher not involved in the recruitment, allocation, or assessment of the participants. Randomization lists will be uploaded in RedCap and cannot be viewed or changed during the trial. Group allocation will be performed over the RedCap database. Patients will be allocated after obtaining consent and completing baseline assessments to confirm eligibility.

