#### Body weight changes and safety

To assess the safety of IF during CHT, during which many patients struggle to maintain their weight, changes in BMI will be recorded and compared between groups. Furthermore, regular laboratory assessments of blood values such as hematograms, liver and kidney function will be assessed over the study period. A detailed overview of laboratory values assessed can be found in **Appendix A**. Laboratory values will be accepted if obtained ± 1 day of the planned assessment day (e.g. one day prior to CHT).

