### Statistical analysis

Patients will be randomized to the intervention or control group (1:1) stratified by tumor entity and study site. The primary endpoint, the difference of the mean change of fatigue over a period of three months as measured by the FACIT-FS© score, will be compared between both groups using mixed models. Confounders such as age, type of CHT, neoadjuvant/adjuvant vs metastatic treatment, the Eastern Cooperative Oncology Group performance status (ECOG), histological tumor grade, and Fédération Internationale de gynécologie et d’Obstetrique (FIGO) -stage will be included in the mixed models. Laboratory data, as well as QoL questionnaire-based outcomes will also be assessed using mixed models. Missing data for the primary outcome as well as secondary outcomes with the potential to become main outcomes in subsequent larger trials will be imputed. Where possible, missing questions from FACT^©^ questionnaires will be prorated using the average of the other answers in the subscale (prorated subscale score = [sum of the item scores]*[N of items in subscale]/[N of items answered]) as long as more than 50% of the items are answered. Data will be imputed by drawing values from the distribution of the control group (jump to reference).

A comprehensive summary will be given for primary and secondary endpoints, including absolute and relative frequencies for categorical and binary variables as well as mean and standard deviation or median and interquartile range and minimum-maximum for all data with at least interval scale level. Pathological response rates after neoadjuvant CHT will be compared using the Chi square test. Radiological response rates (complete response, partial response, stable disease, and progressive disease) will be compared between the arms at 3 months and 6 months using the Mann-Whitney-U-tests. The occurrence of any adverse event as well as the occurrence of grade 3 or higher adverse events will be compared between both groups using the Chi square test. And a list of immunological and metabolic parameters will be compared between both groups using the Mann-Whitney-U test. A paired Wilcoxon test will be used to compare the change in BMI over three months between both groups.

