Analyses will be performed as (1) modified intention-to-treat (ITT) population including all patients randomized who have at least received the first chemotherapy cycle. Patients will be analyzed in the group they were randomized to; (2) per-protocol (PP) sets, including all patients who have at least completed one/two/three or all chemotherapy cycles without major protocol violations. Safety will only be assessed in the per-protocol subset. Subgroup analyses will be performed by tumor type and type of CHT regime for groups with an adequately high number of participants. Furthermore, the parameters will be displayed graphically, and appropriate descriptive statistics will be employed. The significance level will be bilaterally set at 5%. 95% confidence intervals will be reported where appropriate. Due to the exploratory nature of secondary outcomes, no adjustments will be made for multiple testing.

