### Sample size

Sample size calculations were based on a recently published study by Bauersfeld et al. assessing short-term fasting during chemotherapy of breast and ovarian cancer patients (13). A sample size of 48 patients per group is necessary to detect a mean difference of 9.1 points on the FACIT-FS^©^ scale with a standard deviation of 13.7 points and a power of 90% and α=0.05 with a two-sided independent t-test. To account for possible drop-outs, a sample size of 55 per group at baseline is planned.

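### A paired Wilcoxon test is named for the between-arm comparison of BMI change, but the two arms are independent and unmatched

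*Protocol article*

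**What the plan says.** The Statistical analysis section assigns BMI its own test: "A paired Wilcoxon test will be used to compare the change in BMI over three months between both groups". The section on body weight changes and safety states the same purpose: "changes in BMI will be recorded and compared between groups".

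The design is described under Study design and setting as a "prospective, two-arm parallel-group, multi-center, open-label, randomized-controlled clinical trial". Under Recruitment and randomization, allocation works as follows: "Variable block randomization stratified by tumor entities and study site will be used to randomly assign participants to intervention or control group (1:1". No matching of individual patients is described anywhere.

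Elsewhere the article uses independent-samples methods for comparisons between arms. Directly before the BMI sentence it says that "a list of immunological and metabolic parameters will be compared between both groups using the Mann-Whitney-U test". Radiological response gets the same test, and the sample size rests on an independent t-test.

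**The concern.** A paired Wilcoxon (signed-rank) test works on differences within pairs. The pairs must come from the design: two measurements on one patient, or two matched patients. Here the only natural pairs are each patient's baseline and three-month values. Once these have been turned into a change, comparing the changes of two separate groups is a two-sample problem.

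The BMI comparison is meant to show whether fasting adds to weight loss during chemotherapy. Weight may change in both arms, so only a contrast between arms can attribute a difference to fasting. An analyst who follows the sentence to the letter has no valid way to obtain that contrast. The easiest way out, one paired test per arm, answers a different question. It also invites the reader to treat significance in one arm but not the other as a difference between diets.

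**Working it through.** **Inputs from the article.** Two independent arms, 1:1; two-sided 5% level; 48 evaluable patients per group, 55 randomised. No mean, SD or target difference for BMI is given.

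**The article's own figure.** The only calculation in the article is for fatigue: "A sample size of 48 patients per group is necessary to detect a mean difference of 9.1 points" on the FACIT-FS, "with a standard deviation of 13.7 points and a power of 90% and α=0.05 with a two-sided independent t-test". With the normal approximation, n = 2 × (1.960 + 1.282)² × (13.7 / 9.1)² = 2 × 10.507 × 2.2665 = 47.6, so 48 per group. The exact t calculation gives 48.6, and power at 48 is 89.6%. The figure reproduces, and it already assumes independent arms. It is used below only to set the number of patients per arm.

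**What the paired test could mean.**

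1. *Pairing across arms.* Each fasting patient would be paired with some control patient, but the design does not say which. In one simulated data set (48 per arm, true difference 0.5 SD), 5,000 random pairings gave p-values from 3.5 × 10⁻⁸ to 2.3 × 10⁻³, where the Mann-Whitney test gave 1.1 × 10⁻⁴. All were below 0.05 in that data set, but the reported p-value depends on an arbitrary choice. With unequal arms, such as 48 and 47, the test cannot be computed.
2. *Pairing within patients.* The test is run in each arm, baseline against three months. This tests each arm's change against zero, not the difference between arms.

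**Behaviour of the second reading.** Assumptions: normally distributed changes, equal SD, 48 per arm, two-sided 5%. Shifts are in units of the SD of individual BMI change and are assumed, because the article gives none.

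If both arms have the same true change and each within-arm test has power p, the probability that exactly one is significant is 2p(1 − p), with a maximum of 0.5 at p = 0.5. Simulation (3,000 replicates):

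| Same true change in both arms (SD) | Exactly one arm significant |
|---|---|
| 0 | 9% |
| 0.1 | 18% |
| 0.2 | 38% |
| 0.3 | 51% |
| 0.4 | 38% |
| 0.5 | 17% |
| 0.6 | 4% |
| 0.7 | under 1% |

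The 51% lies above the ceiling of 50% only through simulation error: the standard error is √(0.25 / 3,000) = 0.9 percentage points. Repeat runs gave 36% to 39% at 0.2 SD, 50% to 51% at 0.3 SD and 36% to 38% at 0.4 SD. As a check on the formula, at 0.5 SD the simulated within-arm powers were 0.909 and 0.907, and 0.909 × 0.093 + 0.907 × 0.091 = 0.167, which agrees with 17%.

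In the same no-difference setting, the Mann-Whitney test on individual changes rejects in 4.8%, 5.4% and 4.9% of trials at 0.2, 0.3 and 0.4 SD, and in 4.6% at 0.5 SD.

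The opposite failure also occurs. If the arms truly differ by 0.5 SD (−0.25 against +0.25), each within-arm test is significant in about 38% of trials, while the Mann-Whitney test detects the difference in about 66%.

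**The case against.** The strongest defence is that the sentence names the right comparison and only the word for the test is wrong. The authors use the unpaired rank test one sentence earlier, so the phrase may be a slip for the Wilcoxon rank-sum test, or shorthand for the baseline-to-three-month pairing within each patient. With unequal arms an analyst could not run the literal test and would notice. This is plausible, but it does not cure the text: the first reading replaces the stated test, and the second does not deliver the stated comparison.

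Three stronger readings are tempting, and the documents do not support them.

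- A reader might infer a false-positive rate of 36% to 50%. That range holds only for assumed shifts of 0.2 to 0.4 SD, close to the maximum of 2p(1 − p). It is also not the type I error of any planned analysis, because the article nowhere plans to infer a group difference from significance in one arm only. Setting it against the 5% of the Mann-Whitney test compares unlike things. Under arbitrary pairing with equal arms, the simulated type I error was 4% to 6%, which is not inflated.
- A reader might infer that the trial cannot address body weight at all. The Statistical analysis section also promises descriptive summaries for secondary endpoints, graphical display and 95% confidence intervals where appropriate. Only the planned between-arm test is affected.
- A reader might take BMI as the sole safety measure. The article also lists blood counts, liver and kidney function, and CTCAE toxicities.

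**Conclusion.** The point holds as a mismatch between the named test and the stated comparison. It follows from the design alone and needs no numerical assumption. Its practical size is conditional: under an identical true change, 48 per arm and normal changes, significance in exactly one arm occurs in under 1% to about 51% of trials for shifts of 0 to 0.7 SD, and this does harm only if it is read as a difference between groups.

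The sentence should be fixed, but the error is not critical. BMI change is a secondary safety outcome, the article treats secondary outcomes as exploratory, and the primary fatigue analysis, sample size and data collection are untouched.

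**What to change.** Replace the BMI sentence along these lines: *each patient's change in BMI from baseline to three months will be compared between the randomised groups with a two-sided Mann-Whitney U test, and the difference between groups will be reported with a 95% confidence interval.* The Hodges-Lehmann estimate goes naturally with that test.

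If a paired test is kept, label it as a description of change within each arm, and state that it is not used to compare the arms.

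A model of three-month BMI adjusted for baseline BMI, tumour entity and site would be an optional upgrade. It is not needed to cure the error.

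The cost is one sentence, before the analysis is run. No further patients, visits or measurements are required.

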#### Chemotherapy-related toxicities

To assess the effect of IF on chemotherapy-related toxicities (hematological and non-hematological toxicities), the incidence and severity of treatment-related adverse events (AEs) will be recorded by the Common Terminology Criteria for Adverse Events (CTCAE, v5.0). Laboratory measures focused on hematological toxicities, renal and liver functions as well as specific biomarkers for metabolism and tumor immunology (see **Table 1**) will be analyzed during the whole study period.

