### Data monitoring, interim analysis and trial termination

Data will be collected on a personalized case report form at the predefined time points depicted in **Table 1**. Data will be entered in a protected database (RedCap). Only authorized members of the IFAST study team will be allowed to enter, store and access participant data. Paper-based data will be stored at the department of obstetrics and women’s health at the University Medical Center Mainz. Clinical routine data assessments will be stored in the respective patient’s clinical files at the University Medical Center Mainz and St. Josef’s Hospital.

The safety of IF has been proven in many smaller studies, including our pilot trial (9) for healthy people as well as patients under chemotherapy (25). No severe adverse events were observed; thus, no interim analysis is planned. The trial can be terminated by the patient at any time without the risk of negative consequences by withdrawing consent. The discontinuation of the intervention can be decided upon by the investigator due to medical reasons, including the reduction of the BMI to <18 kg/m^2^, acute severe CHT induced side-effects requiring hospitalization or acute, severe non-chemotherapy related medical illnesses requiring hospitalization. Patients terminating the intervention will be asked to fill out the questionnaires outside of the study protocol.

A data monitoring committee consisting of a medical doctor and a study nurse will be overseeing the study visit schedules. All investigators will be obliged to report any changes or deviations of the protocol to the data monitoring committee. Any serious adverse events will be reported to the data monitoring committee and discussed with the principal investigator within 48 hours of occurrence. The termination of the trial for the participant can be decided upon based on the criteria mentioned above by the principal investigator. The termination of the whole trial can be determined by the principal investigator together with the data monitoring committee due to unexpected serious adverse events based on the intervention or due to failure to recruit the planned number of patients.

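### Assessing safety only in the per-protocol subset makes the safety comparison non-randomised and may bias it, probably in favour of intermittent fasting

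*Protocol article*

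**What the plan says.** The Statistical analysis section defines two kinds of analysis set. The first is the "modified intention-to-treat (ITT) population including all patients randomized who have at least received the first chemotherapy cycle", analysed as randomised. The second is the per-protocol sets, "including all patients who have at least completed one/two/three or all chemotherapy cycles without major protocol violations". It then assigns safety to the second kind alone: "Safety will only be assessed in the per-protocol subset".

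The same section plans the adverse event comparison: "The occurrence of any adverse event as well as the occurrence of grade 3 or higher adverse events will be compared between both groups", by chi-square test. Under Body weight changes and safety, "changes in BMI will be recorded and compared between groups", alongside laboratory values.

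Under Data monitoring, interim analysis and trial termination, the investigator may end the intervention for medical reasons, "including the reduction of the BMI to <18 kg/m^2^, acute severe CHT induced side-effects requiring hospitalization", or hospitalisation for another acute severe illness. Patients who stop are asked to go on filling in questionnaires; nothing is said there about further recording of adverse events.

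The fasting schedule applies to the intervention arm only (Intermittent fasting group). The control arm has no dietary restrictions (Control group), and the adherence diary is kept in the fasting arm only (Table 1, footnote 6).

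**The concern.** A safety comparison keeps the protection of randomisation only if patients are counted whatever happens to them later. Here the entry condition is itself an outcome. A patient who loses too much weight or is hospitalised with severe toxicity may stop the diet or fail to complete cycles, and may then leave the set in which weight loss and grade 3 or higher events are compared. Completing chemotherapy is also something the trial hopes to influence: the Introduction expects fewer treatment terminations with fasting.

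The two arms do not face the same filter. Both can fail to complete cycles, but only the IF arm can break a fasting schedule.

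Tolerance of chemotherapy is in the trial's title, safety is a stated purpose in the outcome sections and the Discussion, and no interim analysis is planned. The final between-arm comparison is therefore the main randomised evidence on harm that the trial can give, and the rule replaces it with a selected comparison.

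**Working it through.** **Is there a wider safety set elsewhere?** No section of the article provides one. Serious adverse events go to the data monitoring committee, but that is case handling and does not return an excluded patient to the between-arm comparison.

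**The plan's own figure.** The article gives no safety calculation. Its only calculated figure is the sample size, which sets the arm size used below. With difference 9.1, SD 13.7, 90% power and two-sided alpha 0.05: n = 2 × (1.960 + 1.282)² × (13.7/9.1)² = 47.6, so 48 per group, as stated (an exact t-test gives 48.6, so 49). The planned 55 per group implies a drop-out of 1 − 48/55 = 12.7%. The safety point does not depend on these figures.

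**Effect of the restriction.** Let p be the true event rate in an arm, e1 the share of patients with an event who are removed from the set, and e0 the share of event-free patients who are removed. The rate seen in the per-protocol set is

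p(1 − e1) / [p(1 − e1) + (1 − p)(1 − e0)].

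The article gives none of p, e1 or e0. All values below are assumptions that show the range.

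*Exclusion in the IF arm only, linked to harm (e0 = 10%), control rate 30%:*

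| e1 in IF | IF rate seen, true 30% | Difference seen, true 0 | IF rate seen, true 40% | Difference seen, true +10 |
|---|---|---|---|---|
| 20% | 0.24/0.87 = 27.6% | -2.4 | 0.32/0.86 = 37.2% | +7.2 |
| 30% | 0.21/0.84 = 25.0% | -5.0 | 0.28/0.82 = 34.1% | +4.1 |
| 50% | 0.15/0.78 = 19.2% | -10.8 | 0.20/0.74 = 27.0% | -3.0 |

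Differences are IF minus control, in percentage points. In the last row about 43 (true 30%) or 41 (true 40%) of the 55 IF patients remain, and a true excess of 10 points changes sign.

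*Other patterns:*

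- Controls with an event also drop out (20% of them, no event-free controls), with IF at 50%/10%: the control rate seen is 0.24/0.94 = 25.5%. A true 0 becomes 19.2 − 25.5 = -6.3; a true +10 becomes 27.0 − 25.5 = +1.5, a shift of -8.5.
- Same harm-linked exclusion in both arms (50%/10%): a true 0 stays 0, but a true +10 shrinks to 27.0 − 19.2 = +7.8.
- Exclusion unrelated to harm (10% of IF patients with or without an event): no bias.
- Event-free IF patients excluded more often (30%, against 10% of those with an event): the IF rate seen is 0.27/0.76 = 35.5%, so a true 0 becomes +5.5, against IF.

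**The case against.** The strongest reply is that the direction is not established, and that stands. A reader might infer that harmed IF patients necessarily drop out and that IF will look safer than it is. The article does not show this. Stopping for low BMI or hospitalisation is an option that the protocol itself provides, and Feasibility and adherence counts major violations and discontinuations as separate items, so a permitted medical stop is not shown to be a major violation. A patient harmed after the first cycle could remain in a one-cycle per-protocol set. Controls can also fail to complete cycles because of toxicity; if fasting improves tolerance as hoped, more controls than IF patients could be lost.

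A reader might also take the 20% protocol completion cited in the Introduction to mean that only 11 of 55 IF patients would count. That figure comes from a fasting-mimicking diet that patients disliked, while this schedule allows two days off per week and the group's own trial in a generally healthy population reports 90% compliance. Adherence is in any case not the same as per-protocol membership.

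Scope is open to argument as well. Body weight and laboratory values stand under a heading that names safety, and CTCAE events under a separate heading on toxicities. If safety means only the former, the adverse event tests might escape the restriction. The problem would then remain for BMI, which is both a safety outcome and a reason to stop.

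Two further inferences are not supported. The trial is open-label, but the article does not say who attributes adverse events, so biased attribution cannot be claimed. And which of the per-protocol sets would carry safety is a detail that the full protocol may settle.

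It can also be said that secondary outcomes are exploratory, that the primary endpoint is untouched, and that serious events are reported for all patients. These limit the damage but do not repair the comparison.

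**Conclusion.** The rule is wrong as written. It is an explicit instruction with the word only, not a gap left to another document, and it conditions the safety comparison on post-randomisation events that overlap with the outcomes compared.

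That the comparison is not randomised follows from the text. That it favours IF is probable, because the stopping reasons are harms and only the IF arm has a schedule to violate, but it is not certain. Under assumed rates with IF-only, harm-linked exclusion, a true difference of 0 becomes about -2 to -11 percentage points, and a true +10 becomes +7.2 to -3.0. The bias is nil if exclusion is unrelated to harm and reverses if event-free IF patients are excluded more often. The true figure depends on exclusion rates that the article does not give. The sample size and the primary analysis are not affected.

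**What to change.** Replace the sentence in the Statistical analysis section with a rule to this effect: the primary safety analysis (adverse events, BMI, laboratory values) includes all randomised patients who received the first chemotherapy cycle, by assigned arm, and counts events that occur after the diet is stopped; per-protocol safety is supplementary only. The population is the modified intention-to-treat set already defined there. Naming the three outcome groups also settles what the word safety covers.

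The cost is small but more than one sentence. The section on data monitoring and termination mentions only questionnaires for patients who stop the intervention, and describes these as outside the study protocol. It should state that recording of adverse events, weight and laboratory values continues to the end of the planned follow-up for those patients. This should be settled early, because follow-up that was not recorded cannot be recovered at the analysis. The sample size does not change.

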#### Intermittent fasting group

To increase the feasibility of IF during CHT, the intervention group will be asked to follow an IF schedule of at least 16 h continuous fasting per day on a minimum of five days per week. This allows a disruption of the fasting due to chemotherapy-related issues or to accommodate everyday events such as birthdays or short visits in the IF schedule. We have successfully tested this fasting routine in a pilot study of healthy volunteers, where ketone bodies reached the desired concentration after 16 hours of fasting. We found IF to be safe and effective in reducing fatigue and increasing QoL even in healthy volunteers. The IF schedule was feasible in a stressful work environment and variable working hours during shift work (9). To ensure the positive benefits during the administration of CHT, participants will be required to adhere strictly to the 16h fasting period per day from two days before until one day after the administration of i.v. CHT. To prevent possible negative effects from reversing the metabolic switch to an anabolic state once eating again, no food intake will be allowed on the day of CHT. On the remaining time period of the cycle, the two days of non-fasting per week are allowed. The 16-hour continuous fasting interval can be started at any time point each day. While adhering to the same fasting schedule each day is recommended (e.g., fasting in the morning) to establish behavioral manners, this is not compulsory. Non-sugary drinks including water, tea or coffee without milk (soy milk, oat milk, cow milk etc.), as well as clear vegetable broth are allowed during the 16h fasting period. Within the non-fasting period of 8 hours per day no dietary restrictions will be given. However, a normo-caloric Mediterranean diet are recommended for all patients. Participants of the intervention group will receive a 20-minutes one-on-one counselling by a licensed dietician.

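### Safety is analysed only per protocol, so patients who stop fasting or chemotherapy because of harm can drop out of the safety comparison

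*Protocol article*

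**What the plan says.** The Statistical analysis section defines two kinds of analysis set. The modified intention-to-treat set is described as "including all patients randomized who have at least received the first chemotherapy cycle", with patients kept in their randomised group. The per-protocol sets are described as "including all patients who have at least completed one/two/three or all chemotherapy cycles without major protocol violations". The section then adds: "Safety will only be assessed in the per-protocol subset". It does not say which of the several per-protocol sets is meant.

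The outcomes affected are described elsewhere in the article:

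- Body weight changes and safety: "changes in BMI will be recorded and compared between groups", together with blood counts and liver and kidney function.
- Statistical analysis: any adverse event is tested between arms, and "the occurrence of grade 3 or higher adverse events will be compared between both groups using the Chi square test".

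Two other sections bear on who ends up in a per-protocol set:

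- Intermittent fasting group: around each infusion "participants will be required to adhere strictly to the 16h fasting period per day", and nothing may be eaten on the infusion day. The Control group section sets no dietary restriction.
- Data monitoring, interim analysis and trial termination: "discontinuation of the intervention can be decided upon by the investigator due to medical reasons, including the reduction of the BMI" below 18 kg/m², or "acute severe CHT induced side-effects requiring hospitalization".

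**The concern.** A safety comparison should keep the patients who were harmed. Here the set is chosen by criteria that harm itself can trigger, in two ways.

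1. **Major protocol violation.** Only the fasting arm can break a fasting rule. If stopping or breaking the diet because of weight loss, toxicity or intolerance counts as a major violation, those patients leave the comparison and no matching controls leave by that route. The article does not define a major violation, so this is a risk and not a certainty.
2. **Completed cycles.** In the set that requires all cycles, any patient in either arm who ends chemotherapy early for toxicity is excluded by construction. A patient whose toxicity stops her within cycle 1 is in none of the sets. Yet the Introduction names fewer treatment terminations as a possible benefit of fasting.

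The trial intends to draw conclusions about both the safety of fasting and its effect on chemotherapy toxicity. Dropping fasting patients who did badly could hide harm and could also produce the benefit that is hypothesised. The Feasibility and adherence section counts discontinuations, but a count does not put the adverse events and weights behind them into the comparison.

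**Working it through.** **The plan's own figure.** The Sample size section gives 48 per group for a difference of 9.1, SD 13.7, 90% power and two-sided α of 0.05. The normal approximation gives 2 × (1.960 + 1.282)² × 13.7² / 9.1² = 47.6, so 48. The plan enrols 55 per group. This figure is reproduced but does not bear on the point; only the 55 per arm is used below. The article gives no adverse event rates, so every rate here is an assumption.

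**Adverse events.** Let pF and pC be the true risks of a grade 3 or higher event in the fasting and control arms, and h the share of fasting patients with an event who are excluded. The control arm is taken as complete. The fasting risk seen per protocol is

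pF(1 − h) / (1 − pF·h).

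For example, with pF = 0.30 and h = 0.25: 0.225 / 0.925 = 0.243, so the apparent difference from a control risk of 0.30 is −5.7 points.

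| True risks (fasting vs control) | True difference | h = 0.10 | h = 0.25 | h = 0.50 |
|---|---|---|---|---|
| 30% vs 30% | 0 | −2.2 | −5.7 | −12.4 |
| 40% vs 30% | +10 | +7.5 | +3.3 | −5.0 |
| 50% vs 30% | +20 | +17.4 | +12.9 | +3.3 |

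- With equal true risks anywhere from 20% to 50%, the false benefit is 1.6–2.6, 4.2–7.1 and 8.9–16.7 points for the three values of h.
- A true excess vanishes at h = (pF − pC) / (pF(1 − pC)). For 40% vs 30% this is 0.10 / (0.40 × 0.70) = 0.357, or 55 × 0.40 × 0.357 = 7.9 patients.
- For 50% vs 30%, simulated chi-square power to show harm (8,000 trials) falls from 58% with all patients to 46%, 28% and 6%.

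**A second parameterisation.** Let f be the share of the fasting arm excluded and a the risk among those excluded. The per-protocol risk is (p − f·a) / (1 − f). Take f = 7/55 = 12.7%, the plan's own dropout allowance, with a between 70% and 100%.

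- True risk 40% in both arms: the fasting risk appears as 35.6% to 31.2%, a false benefit of 4.4 to 8.8 points. At f = 20% it is 7.5 to 15 points.
- True risk 50% vs 40%: the 10-point excess shrinks to 7.1 to 2.7 points. At f = 20% it becomes +5.0 to −2.5, so the sign can reverse.
- If a = p, the result is unchanged and there is no bias.

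**Weight.** This was simulated in 4,000 trials with 55 per arm. Baseline BMI had mean 27, SD 5 and minimum 19. Percent weight change was linear to week 12, with mean −1, patient SD 4 and noise SD 1, and visits at weeks 3, 6, 9 and 12. In the fasting arm, 20% of patients lost a further 10 percentage points.

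| Fasting patients excluded | Mean number of 55 | Week-12 difference (points) | Mann-Whitney power |
|---|---|---|---|
| None | 0 | −2.0 | 39% |
| All crossing BMI 18 | 0.5 | −1.9 | 37% |
| Half of those passing a 5% loss | 9.0 | −0.7 | 7% |
| Half of those passing a 7% loss | 6.3 | −0.9 | 11% |
| Half of those passing a 10% loss | 3.6 | −1.3 | 20% |

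The written BMI rule alone is therefore trivial. A material bias in weight needs patients to stop or break the diet by other routes.

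**Precision.** The Introduction cites compliance of 20% (a fasting-mimicking diet during chemotherapy) and 90% (this diet, in the group's own earlier trial). Applied to 55 patients, these leave 11 and 49.5, taken as 50. With no events seen, the one-sided 95% upper limit is 1 − 0.05^(1/n). The chance of seeing at least one event of 5% risk is 1 − 0.95^n.

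| n | Upper limit | Chance of at least one event |
|---|---|---|
| 11 | 23.8% | 43% |
| 50 | 5.8% | 92% |
| 55 | 5.3% | 94% |

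**The case against.** Several points can be made for the plan.

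- **Scope.** The article uses the word safety in its heading on body weight and laboratory values. Adverse events sit under a separate toxicity heading and could be read as analysed in both sets. That reading is possible, but adverse events are commonly called safety and the article does not settle the matter. The restriction applies to weight and laboratory values on either reading.
- **Undefined violation.** Stopping for low BMI or hospitalisation is permitted, so it may not be a violation, and two days off per week are allowed outside the chemotherapy window. This limits the certainty of the first route but does not close it.
- **Nested sets.** If safety used the one-cycle set, a patient stopping chemotherapy later for toxicity would stay in. The text does not choose that set, and the no-violation condition would still apply. The completed-cycles route also works in both arms, whereas the calculations assume a complete control arm, so they describe one-sided exclusion only.
- **Serious adverse events** go to the data monitoring committee whichever set is analysed. That protects individual patients, but it is case reporting and not a comparison of arms.
- **Size.** Excluding half of the patients with events and retaining only 20% are extreme cases. The 20% comes from a different diet, whose components patients disliked. At 90% retention the loss of precision is negligible.
- **Test.** The weight calculation uses a Mann-Whitney test, while the article names a paired Wilcoxon test. A paired test does not compare two independent arms, so the calculation used the rank test that does.

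These points limit how large and how certain the bias is. None supplies a safety analysis of all treated patients.

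**Conclusion.** The concern holds. The restriction is explicit, it selects on events after randomisation that harm can cause, and no other part of the article provides a between-arm safety comparison in all treated patients.

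The size of the bias is unknown. Under one-sided exclusion and the assumed event rates, shifts in the grade 3 or higher comparison run from about 2 points to more than 10 in favour of fasting. Losing about 8 of 55 patients, all with events, is enough to erase a true 10-point excess. The bias is nil if exclusions are unrelated to harm, and negligible for weight if only the BMI threshold leads to exclusion. The primary fatigue endpoint is not affected. The plan should still be changed, because its safety conclusion depends on this choice and a better set is already defined.

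**What to change.** In Statistical analysis, replace the sentence on safety with wording such as: *Safety, including BMI change and adverse events, will be assessed in all randomised patients who received the first chemotherapy cycle (the modified intention-to-treat set), in the group to which they were randomised, whether or not they stopped the diet or chemotherapy. Per-protocol results are supplementary.*

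In Data monitoring, interim analysis and trial termination, add that weights and adverse events recorded at routine chemotherapy visits after the diet is stopped enter the safety analysis. That section now mentions only questionnaires for these patients, so the clause is needed to make sure the data are carried into the trial database.

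The cost is one sentence and one clause, with no new visits or measurements and no change in sample size. The drawback is that the estimate becomes the effect of being assigned to fasting, which is diluted if patients who stop regain weight or recover. The supplementary per-protocol result still describes those who kept to the diet.
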